### ***Anamorelin for anorexia, V1.6, 07 April 2022***

### ***Timed up and go test***

The Timed Up and Go (TUG) test is a functional mobility test that requires the patient to stand up, walk 3 metres, turn, walk back and sit down. The presence of slowness, hesitancy, abnormal trunk or arm movements, staggering or stumbling is used to grade the patient from 1 (normal) to 5 (severely abnormal). A score of 3 (mildly abnormal) or more suggests a risk of falling. A slow time suggests an increased risk of falls. The test will be conducted at: baseline (Visit 2), and Weeks 4, 8 and 12 (Visits 3, 4 and 5), and at Weeks 18 and 24 for those participating in the optional extension phase (Visits 6 and 7).

## **6.7 Patient reported symptom measure**

### ***Functional Assessment of Anorexia/Cachexia Therapy (FAACT)***

The functional assessment of anorexia/cachexia therapy (FAACT) questionnaire is an instrument for diagnosing anorexia. There are 12 items on the FAACT that are related to the patient's appetite in the last seven days. Each item is scored on a five-point Likert scale (zero equates to not at all and four equates to very much). From this questionnaire the 5-item section referring to anorexia symptoms will be used to assess primary efficacy endpoint. The assessment will be filled out by patients at every visit: screening (Visit 1), baseline (Visit 2) and at Weeks 4, 8 and 12 (Visits 3, 4 and 5) as well as during optional extension phase at Weeks 18 and 24 (Visits 6 and 7).

### ***Global Impression of Change***

This participant rated seven-point scale (1-7) provides information about the participant perception of their change in clinical status, specifically their improvement since the commencement of the study. 1 = "Very much improved" 2 = "Much improved," 3 = "Minimally improved," 4 = "No change" 5 = "Minimally worse," 6 = "Much worse," or 7 = "Very much worse." The results of this scale over the study period will assist to determine the clinical significance of any improvement seen. The assessment will be filled out by patients at Weeks 4, 8 and 12 (Visits 3, 4 and 5) and at Week 24 during the optional extension phase (Visit 7).

### ***EuroQol 5-Level 5-Dimensions – Quality of Life***

Quality of life of participants will be measured using the EQ-5D-5L. There is currently no single agreed measure of health-related quality of life in palliative care populations. EQ-5D-5L assesses mobility, self-care, usual activities, pain / discomfort, anxiety / depression according to three levels of severity (1 = no problems; 2 = some

or moderate problems; 3 = extreme problems), plus a VAS of current health-related quality of life, scored 0 – 100. This will be administered to patients at baseline (Visit 2), Weeks 8 and 12 (Visits 4 and 5) as well as during optional extension phase at Week 24 (Visit 7).

#### ***ICECAP-A – ICEpop CAPability measure for Adults***

ICECAP-A is a measure of capability for the general adult (18+) population for use in economic evaluation. It focuses on wellbeing defined in a broader sense, rather than health and comprises five attributes: attachment (ability to have love, friendship and support), stability (ability to feel settled and secure), achievement (ability to achieve and progress in life), enjoyment (ability to experience enjoyment and pleasure) and autonomy (ability to be independent). The ICECAP-A will be administered to the participants after the EQ-5D-5L questionnaire at baseline (Visit 2) and Weeks 8 and 12 (Visits 4 and 5), as well as during optional extension phase at Week 24 (Visit 7). It will probe valuable additional, symptom-specific information to the EQ-5D-5L. Its use in the study may also give insight into which QoL questionnaire participants find more acceptable.

#### ***Short Questionnaire to Assess Health Enhancing Physical Activity – SQUASH***

Physical activity undertaken and participant adherence to physical activity advice will be recorded by patients using the Short Questionnaire to Assess Health Enhancing Physical Activity – SQUASH. This tool was developed to give an indication of the habitual activity level. The SQUASH contains questions on multiple domains referring to an average week in the past month: commuting activities (walking, cycling), household activities, leisure time (sports, walking, gardening, cycling) and activities at work or school. The assessment will be filled out by patients at baseline (Visit 2), Weeks 4, 8, and 12 (Visits 3, 4 and 5) as well as during the optional extension phase at Weeks 18 and 24 (Visits 6 and 7). Increase in physical activity will be reviewed over the study period. A traffic light system for progression criteria assessment will be used whereby >40% indicates that the criteria have been met (green), 30-40% indicate that some changes should be made to the larger trial (orange) and <30% indicates that a further trial should not proceed (red).

#### ***Functional Assessment of Chronic Illness Therapy-Fatigue (FACIT-F)***

Fatigue is a disruptive symptom that inhibits normal functional performance. The functional assessment of chronic illness therapy-fatigue (FACIT-F) scale is a tool that measures the individual's level of fatigue during their usual daily activities over the past week. The FACIT-F scale is a 13-item scale and the level of fatigue for each item is measured on a four point Likert scale (four equates to not at all fatigued and zero equates to very much

fatigued), the range of possible scores is 0-52. The assessment will be filled out by participants at baseline (Visit 2) and Weeks 8, and 12 (Visits 4 and 5) as well as during the optional extension phase at Week 24 (Visit 7).

### ***Participant diary***

Participants will be asked to record daily step counts as described above. Adherence to dietary advice is a feasibility measure in this trial and will be assessed by asking participants to keep a food diary of everything they eat and drink for 3 complete days preferably prior to study visits, including, when possible, 2 weekdays and 1 weekend day (e.g. Thursday, Friday and Saturday). Participants will be encouraged to bring their complete food tracking diary during each visit. If participants do not complete the 3-day food diary prior to visits, a 24-h diet recall will be collected by the study nurse at the time of visit. Any increase in macronutrient intake will be reviewed over the study period. A traffic light system for progression criteria assessment to a larger phase 3 study will be used whereby >40% indicates that the criteria have been met (green), 30-40% indicate that some changes should be made to the larger trial (orange) and <30% indicates that a further trial should not proceed (red). The contents of the food diary will be entered into a dietitian directed database in order to analyse if the food intake recorded within the diaries complies with the dietary advice provided to each participant.

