### **1.3 Existing evidence of anamorelin for anorexia**

Ghrelin is an endogenous stimulator of appetite by targeting the growth hormone secretagogue receptor (GHSR-1a). Similar to ghrelin, anamorelin increases GH, insulin-like growth factor-1, and insulin-like growth factor binding protein-3 thus producing the desired effect of significant appetite stimulation. Two international, phase III trials (ROMANA 1 [HT-ANAM-301] and ROMANA 2 [HT-ANAM-302]) and an associated extension study (ROMANA 3 [HT-ANAM-303]) tested anamorelin for cancer anorexia and cachexia in people with stage III and IV NSCLC. These placebo-controlled trials, which included a total of over 900 patients, demonstrated that anamorelin safely reversed muscle loss, augmented body weight and was associated with clear improvements in appetite. The trials failed to meet functional co-primary endpoint (in this case, hand-grip strength, which was a requirement for approval in Europe and the USA) but showed that anamorelin was well tolerated and sustainably improved appetite in the majority of participants, a finding not seen in the placebo control arm. That said, in these trials food intake was not recorded and it is not known if the improvement in anorexia translated into an adequate nutritional intake. Therefore, despite promising findings, anamorelin has not been approved by the Therapeutic Goods Administration (TGA) in Australia or the Food and Drug Administration (FDA) in the US for use in cancer anorexia. The main regulatory concern has been the lack of reliable and clinically meaningful endpoints in these trials to show relevant effect on patient functioning and quality of life. By contrast, this proposed feasibility study uses a combination of participant-reported measures (appetite) and objective measures directly related to potentially improved health outcomes (improved ability to tolerate and complete anti-cancer therapies on-time and on-dose). These end-points relate directly in the proposed study to outcomes that can deliver improved overall health and wellbeing. Recently, the use of anamorelin for improvement of weight loss and anorexia in cancer cachexia in people with NSCLC, gastric cancer, pancreatic cancer and colorectal cancer was approved in Japan, a world first. Consequently, there is considerable expected value from the current proposed trial which includes endpoints relevant to completing disease-modifying cancer therapy and better maintaining functional status.

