## 5.0 OUTCOMES AND MEASURES

### 5.1 Primary Outcome

#### 5.1.1 Feasibility

Progression criteria will be assessed using an indicative traffic light system (green, orange red) whereby green (go) suggests that the criteria have been met and the trial should proceed, orange (amend) indicates that some changes should be made to the larger trial and red (stop) indicates that a larger trial should not proceed. Feasibility will be assessed by evaluating:

1. **Recruitment rate**, defined as an average of one participant per site (six sites) every six weeks – plan to recruit 50 participants.
2. **Proportion of participants with complete primary endpoint data** – >70% (green), 60-70% (orange), <60% (red).
3. **Participant adherence to investigational medication** – >70% (green), 60-70% (orange), <60% (red).
4. **Participant adherence to physical activity advice**, as measured by the Short Questionnaire to Assess Health Enhancing Physical Activity (SQUASH), completed at every visit (whereby increase in physical activity will be reviewed over the study period) – >40% (green), 30-40% (orange), <30% (red).
5. **Participant adherence to dietary advice**, as measured by the food diary kept for three days prior to visits (whereby increase in macronutrients intake will be reviewed over the study period) – >40% (green), 30-40% (orange), <30% (red).

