## 10.0 STATISTICS

### 10.1 Power and sample size

A total of 50 participants with small cell lung cancer will be randomised 1:1 to anamorelin HCl 100 mg or placebo in order to have data at 12 weeks on 40 participants (approximately 20 in each treatment arm). Since this is a feasibility study, it is not required to calculate a fully justified sample size for establishing the efficacy of the intervention. It has been suggested, however, that in feasibility studies, a sample size between 24 and 50 is acceptable. The findings from this study will be used to inform the calculation of a sample size for a future larger scale phase III trial.

Participants discontinued after randomisation will not be replaced.

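### The diet and activity adherence criteria are judged by an increase in intake or activity, which is not adherence and, for diet, can include the drug's own effect

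*Supplement*

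**What the plan says.** Section 5.1.1 of the protocol lists five feasibility criteria. Items 4 and 5 are adherence to the physical activity advice, from the SQUASH questionnaire, and adherence to the dietary advice, from the 3-day food diary. Each is explained by a change in the outcome: "whereby increase in physical activity will be reviewed over the study period" for item 4 and "whereby increase in macronutrients intake will be reviewed over the study period" for item 5. Section 6.7 repeats this under SQUASH ("Increase in physical activity will be reviewed over the study period") and under Participant diary ("Any increase in macronutrient intake will be reviewed over the study period"). The word *any* appears for diet only.

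Both items are green above 40%, orange from 30% to 40% and red below 30%. Red means that a larger trial should not proceed. Section 10.3 makes the feasibility thresholds the focus of the primary analysis, and section 5.1.2 makes desirability depend on the feasibility endpoints being met.

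Three other places bear on this:

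- The last sentence of the Participant diary text plans a dietitian-directed database to "analyse if the food intake recorded within the diaries complies with the dietary advice provided to each participant". No band is tied to that analysis.
- Section 1.3 describes the drug as raising growth hormone and related factors, "thus producing the desired effect of significant appetite stimulation".
- Section 5.2.1, item 8, makes nutritional intake from the same 3-day diary a secondary efficacy endpoint.

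**The concern.** The two items are named as adherence, but what is described is a change in intake or activity. Such a change can arise in at least three ways that have nothing to do with following a leaflet.

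- **Drug effect.** Half the participants take a drug expected to stimulate appetite. If it works, their intake rises whether or not they read the advice. One diary measurement then counts both as efficacy and as adherence. This route is direct for diet and only indirect for activity.
- **Noise.** Three diary days, or a single 24-hour recall when the diary was not kept, give an unstable change score. With no true change, a participant may well show an increase by chance.
- **Disease and treatment.** Section 1.2 describes worsening functional capacity in this population. Someone who follows the advice may still eat less and move less at Week 12.

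All participants get the same leaflets (section 4.1), so no arm without advice shows the background rate of increase. The colour could therefore favour or discourage phase III for reasons unrelated to whether patients can follow the advice.

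**Working it through.** The protocol gives no expected adherence rate or operating characteristic for these items, so there is no stated figure to reproduce. The check asks how the colour would behave among participants who do not adhere at all.

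**Inputs from the protocol.** 50 randomised 1:1, with 12-week data expected on 40, about 20 per arm (section 10.1). Bands of 40% and 30% (section 5.1.1). No imputation (section 10.3).

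**Assumptions, not in the protocol.** The percentage is the share of participants with any increase. Each non-adherent participant shows an increase with probability p, independently of the others. Symmetric noise means p = 0.5; background decline means p below 0.5.

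**Step 1: counts needed.** Green (>40%) needs at least 17 of 40 or 21 of 50. Red (<30%) needs at most 11 of 40 or 14 of 50.

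**Step 2: probability of green with zero adherence.** P(green) = P(X ≥ 17), X ~ Bin(40, p), or P(X ≥ 21), X ~ Bin(50, p).

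| p | n = 40 | n = 50 |
|---|---|---|
| 0.30 | 0.063 | 0.048 |
| 0.35 | 0.202 | 0.186 |
| 0.40 | 0.432 | 0.439 |
| 0.45 | 0.681 | 0.714 |
| 0.50 | 0.866 | 0.899 |
| 0.60 | 0.992 | 0.997 |

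**Step 3: probability of red.** At p = 0.5 it is 0.003 (n = 40) or 0.001 (n = 50). At p = 0.25 it is P(X ≤ 11) = 0.715 (n = 40) or P(X ≤ 14) = 0.748 (n = 50). If illness brings p down to 0.25 among people who do follow the advice, the same red rates apply to them.

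**Step 4: the undefined parts of the rule matter.**

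- Denominator: if 50 stays the denominator, 40 are observed and the missing 10 count as non-adherent, green needs 21 of the 40 observed. At p = 0.5 this has probability 0.437 instead of 0.866.
- Time point: if an increase at any one of three follow-up visits counts, p is 3/4 under exchangeable noise, and green at n = 40 has probability above 0.999.

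**Step 5: drug effect on the diet item.** Let control participants have probability p, and let the drug shift the change by d standard deviations, so that p(drug) = Φ(Φ⁻¹(p) + d). Adherence is zero in both arms, with 20 per arm, and the arms are pooled.

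- p = 0.30, d = 0.5: p(drug) = Φ(−0.524 + 0.5) = 0.490. P(green) rises from 0.063 to 0.406.
- p = 0.30, d = 0.8: p(drug) = 0.609. P(green) rises to 0.711.
- p = 0.40, d = 0.5: p(drug) = 0.597. P(green) rises from 0.432 to 0.867.

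The shifts are assumed values chosen to show the direction and scale. The protocol gives no effect on intake.

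**The case against.** A reader might infer that the plan turns green about 90% of the time with zero adherence. The documents do not support that. The figure needs the percentage to be a share of participants, a chance of increase of exactly 0.5, and all 50 analysed. None of these is stated, and the plan expects 12-week data on 40. With background decline, which is plausible in this population, the same reading gives 43% or 6%.

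Nor do the documents say that anyone with an increase is counted as adherent. They say that an increase will be reviewed. *Any* appears for diet only and could mean whatever increase occurs. On this view the fault is an unfinished rule, and for diet a real compliance check is already planned.

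The drug effect is also less than established. Section 1.3 notes that food intake was not recorded in the earlier trials, so it is not known whether better appetite led to adequate intake. For SQUASH, any drug effect is indirect. Finally, the traffic lights are called indicative, and these are two of five criteria.

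These points limit the claim but do not remove it. The only metric described alongside the bands is an increase, and the planned compliance analysis is linked to no band. If the percentage meant the size of the increase, drug and disease effects would still enter. The wide spread of results is itself informative: under this reading the colour follows background trend and missing-data handling.

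**Conclusion.** The concern holds in this form: the two criteria named as adherence are judged by an increase in intake or activity, with no minimum change, time point, denominator or split by arm. An increase does not measure adherence. For diet it can include drug effect, because the drug is expected to stimulate appetite and the same diary is an efficacy endpoint. For both measures, noise or disease decline can drive the result.

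The size is conditional. Reading the percentage as the share with any increase, with symmetric noise and no adherence, green occurs 87% (n = 40) to 90% (n = 50) of the time. At p = 0.40 and p = 0.30 it occurs 43% and 6% of the time (n = 40). At p = 0.25, red occurs 72% to 75% of the time. No single one of these figures is a property of the plan. The protocol should be changed, because the metric affects a primary go/no-go assessment and a better one for diet is already in the text.

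**What to change.** In section 5.1.1 items 4 and 5, section 6.7 and the trial summary:

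- **Diet.** Apply the bands to the result of the dietitian-database compliance analysis, not to an increase in intake.
- **Activity.** Score SQUASH against the activity advice in the leaflet, if the leaflet contains a checkable target. It is not among the documents, so this needs confirming.
- **Rule.** Fix the pass mark, the Week 12 time point and the denominator, including how missing diaries and questionnaires count, before unblinding.
- **Arms.** Report both measures by arm. Read the placebo arm as free of drug effect, though still affected by disease and chemotherapy and imprecise at about 20 people.
- **Efficacy.** Keep change in intake and in activity as exploratory efficacy outcomes only.

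The cost is wording: the diary, database and SQUASH data are already to be collected. The downside is that a pass mark must be written in advance and the 40% and 30% bands confirmed for the new measure. Scoring against the advice does not by itself remove drug or illness effects, which is why the report by arm is needed.

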### ***Unplanned healthcare costs.***

Participants (and caregivers) will also be reminded to record in their diaries resource use to estimate cost of indirect and informal care. This will help assess the proposed measures for a health economic analysis (cost consequence) in any subsequent phase III study. Questions including time off work for patients, caregiver time spend in-home nursing or accompanying to hospital, out-of-pocket expenses, etc. Furthermore, participants will also be asked to record any unplanned healthcare contact/ hospitalisations defined as an emergency admission; or unplanned emergency contact with GP, nurses, specialists, home help visit, etc.; or unplanned readmission within 28 days following discharge to the same facility. These include inpatient/outpatient attendance and community care and participant may arrive at hospital in own transport or in an ambulance. Length of stay with primary reasons will also be asked to be entered in a diary by participants from baseline to Week 12 (or 24).

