## **5.2 Secondary endpoints**

### **5.2.1 Secondary efficacy (clinical assessments proposed for any subsequent phase III study)**

1. Baseline demographic and clinical predictors of responders.
2. Change in body weight and BMI at every visit and assessment of historical stable weight at baseline.
3. Change in lean body mass measured at baseline and week 12 (or 24) by dual x-ray absorptiometry (DEXA) and Bioelectrical Impedance Analysis (BIA).
4. Change in muscle mass at thoracic (T4) level, measured by electronically stored data from computed tomography (CT) scans whenever they are done clinically.
5. Functional status using clinician-rated Australia-modified Karnofsky Performance Scale (AKPS) measured as area under the curve from data collected at every scheduled visit.
6. Timed *up and go test* (TUG) measured at every scheduled visit.
7. Functional performance as measured by a pedometer app (stepapp) or a wearable digital pedometer, for participants who do not have mobiles, worn for two days (preferably one weekday and one weekend day) prior to visits.
8. Nutritional intake measured by self-reported 3-day food diary, including 2 weekdays and one weekend day prior to visits. If participants do not complete the 3-day food diary prior to visits, a 24-h diet recall will be collected by the study nurse at the time of visit.
9. Biochemical changes including C Reactive Protein (CRP), IL-6, albumin and pre-albumin from baseline.
10. Survival (overall and cancer-specific) measured with data of death from the time of enrolment.
11. Changes overtime in the participant rated Global Impression of Change (GIC) and in the clinician rated Clinical Global Impression of Severity and Improvement (CGI-S, CGI-i).
12. Changes overtime in quality of life measured by EQ-5D-5L (EuroQoL five-dimensional instrument) and ICECAP-A (ICEpop CAPability measure for Adults).

13. Changes overtime in participant-reported fatigue as measured by the Functional Assessment of Chronic Illness Therapy-Fatigue (FACIT-F) domain.
14. Rates of unplanned hospitalisations (defined as an emergency admission; or unplanned emergency contact with GP, nurses, specialists, home help visit, etc.; or unplanned readmission within 28 days following discharge to the same facility – participant may arrive at hospital in own transport or in an ambulance) and length of stay; with primary reasons kept in a diary by participants.

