## 6.0 STUDY ASSESSMENTS

The study assessments are tabulated in Table 6-1. The study period will include 28 days after medication cessation (4 weekly follow-up period) or until death (whichever timeframe is shorter).

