| Acceptability of the study and proxy                           |           |          |                                  |   | X*       |           | X        | X                                                       |                            |
| SCLC treatment regimen and dose or interval adjustments        |           | X        | X                                | X | X        | X         | X        | X                                                       | X                          |
| Unplanned healthcare contacts (review diary)                   |           | X        | X                                | X | X        | X         | X        | X                                                       |                            |
| Response to cancer therapy for SCLC and adverse events         |           |          |                                  |   | X        |           | X        | X                                                       | X                          |
| Check compliance (review diary)                                |           |          | X                                | X | X        | X         | X        | X                                                       |                            |
| Dispense (D) new and/or return (R) unused medication for study |           | X
(D) |                                  |   | X
(R) | X
(D)  | X
(R) | X
(R)                                                |                            |

AKPS, Australia-modified Karnofsky Performance Status; BMI, Body Mass Index; ECG, Electrocardiogram; HbA1c, glycated haemoglobin, CPR, C-reactive protein; FAAct, Functional Assessment of Anorexia Cachexia Treatment; DEXA, dual x-ray absorptiometry; CT, computed tomography; FACIT-F, Functional Assessment of Chronic Illness Therapy-Fatigue; SQUASH, Short Questionnaire to Assess Health Enhancing Physical Activity; GIC, Global Impression of Change; CGI-S, Clinical Global Impression of Severity; CGI-I, Clinical Global Impression of Improvement; SCLC, small cell lung cancer. TUG – Timed Up and Go test.

a Occurs after the last dose of the study intervention (last day of data collection, or when treatment is ceased, if cessation prior to Week 12 or Week 24 occurs)

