#### **9.1.5 Serious adverse events**

SAEs are any untoward medical occurrence that: meets one or more of the following criteria/outcomes:

- death;
- life-threatening (i.e. at immediate risk of death);
- in-patient hospitalisation or prolongation of existing hospitalisation;
- persistent or significant disability/incapacity;
- congenital anomaly or birth defect;
- other medically relevant condition judged as serious.

- “Life threatening” means that the participant was at immediate risk of death from the event as it occurred. It does not include an event that, had it occurred in a more serious form, might have caused death.
- “Requires inpatient hospitalisation” is defined as hospital admission for treatment of the AE. Hospital admission for scheduled elective surgery would not be an SAE.
- “Other medically relevant condition judged as serious” is where medical and scientific judgment should be exercised in deciding whether expedited reporting is appropriate in other situations, such as important medical events that may not be immediately life-threatening or result in death or hospitalisation but may jeopardise the participant or may require intervention to prevent one of the other outcomes listed in the definition above. These should also usually be considered serious. Examples of such events are intensive treatment in an emergency room or at home for allergic bronchospasm; blood dyscrasias or convulsions that do not result in hospitalisation; or development of drug dependency or drug abuse. A diagnosis of a new cancer during the course of the treatment should be considered as medically important.

Progression of a participant’s underlying condition leading to one of the above should always be reported as a serious (but expected) AE, which is unrelated to protocol treatment, or caused by failure of the anticipated therapeutic effect of the study drugs/intervention.

The expected study population have an underlying disease that is expected to significantly shorten life expectancy, they are already termed palliative and are expected to die within a short period of time. In this study, a number of SAEs may be anticipated, but these are unlikely to be attributable to the study intervention.

The conditions recognised as being excluded from the usual SAE reporting timeframes (but are still to be recorded as SAEs) are as follows:

- Where participants are admitted as a planned admission due to respite, family or social issues, or for pre-planned treatment.

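### Unplanned admissions and length of stay are taken from a participant-kept diary although site-held SAE and medical records cover them, so admissions shortly before death or withdrawal can drop out of the endpoint

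*Supplement*

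**What the plan says.** Section 2.2.2 lists rates of unplanned health care contact, hospitalisations and length of stay as secondary parameters. Section 5.2.1, item 14, defines the endpoint, "with primary reasons kept in a diary by participants". Section 6.7 (Unplanned healthcare costs) says that "participants will also be asked to record any unplanned healthcare contact/ hospitalisations", and that length of stay with its reasons is to be "entered in a diary by participants from baseline to Week 12 (or 24"). In Table 6-1 the row "Unplanned healthcare contacts (review diary") is marked from baseline to Week 24 and at exit or early termination. Its follow-up cell is blank, although Section 6.0 states: "The study period will include 28 days after medication cessation".

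Other parts of the protocol hold a second record of the same admissions. Section 9.1.5 makes "in-patient hospitalisation or prolongation of existing hospitalisation" an SAE criterion, and admissions exempt from the usual reporting timeframes must still be recorded. Section 9.1.8 runs AE and SAE collection through the 4-week telephone follow-up. Items 15 and 16 of Section 5.2.1 (febrile neutropaenia and chemotherapy adverse events) are drawn from the medical record.

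**The concern.** The endpoint relies on the person least able to supply the data at the moment it matters. Someone admitted as an emergency who then dies, or withdraws because of the illness, may never present the diary covering that admission. The missingness is then related to the event being counted. Section 9.1.5 describes a population with a short life expectancy, so this is not a remote case.

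The consequence would be admission counts and bed-days that are too low. If early death or withdrawal differs between arms, the between-arm comparison would be distorted too. Section 6.7 says that the diary's resource-use data will help assess the measures proposed for a phase III health-economic analysis. An incomplete count could make the measure look less informative than it is.

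**Working it through.** **Inputs.** From Section 10.1: 50 randomised, "in order to have data at 12 weeks on 40 participants (approximately 20 in each treatment arm"). Diary window: 12 weeks without the extension (Section 6.7). Study period: treatment plus 28 days, hence 16 weeks without the extension (Section 6.0). The documents give no event rate and no denominator for these rates.

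**The plan's own figure.** 1 − 40/50 = 20% implied loss, and 40/(1 − 0.20) = 50. The sample size is consistent with 10 participants lacking Week 12 data. The 20% is implied, not stated.

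**Shortfall for events seen only through the diary.** Assume a constant event rate, 40 participants with 12 diary weeks each, and 10 who leave after *t* weeks with their diary reviewed up to then. With all 50 over 12 weeks as denominator:

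shortfall = 1 − (40×12 + 10×*t*)/(50×12)

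- *t* = 0: 1 − 480/600 = 20%
- *t* = 4: 1 − 520/600 = 13%
- *t* = 6: 1 − 540/600 = 10%
- *t* = 8: 1 − 560/600 = 7%

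**Sensitivity to informative loss.** If the 10 have *k* times the event rate of the others, the share missed is 10*k*(12 − *t*)/(480 + 120*k*). With *k* = 2, which is an assumption, this is 80/720 = 11% at *t* = 8 and 240/720 = 33% at *t* = 0. Against this, Section 6.0 ends the study period at death, so time after death is not missed time. Where loss is by death, only the interval from the last reviewed diary to death is unobserved.

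**If the 28-day follow-up were also in the denominator.** With complete retention and no extension, 1 − 12/16 = 25%. With all 50 over 16 weeks, the result runs from 1 − 560/800 = 30% (*t* = 8) to 1 − 480/800 = 40% (*t* = 0). With everyone completing the extension, 1 − 24/28 = 14%. The plan does not state such a denominator.

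**Effect of the remedies.** Dividing by observed diary time removes the shortfall at a constant rate (0%). It does not help if the unobserved days are those with more admissions, which is why the source has to change for admissions. If site records recover a share *s* of the admissions in a gap *g*, the remaining shortfall is *g*(1 − *s*). A 20% gap becomes 10% at *s* = 0.5 and 4% at *s* = 0.8 (values of *s* assumed).

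**The case against.** The strongest reply is that admissions are not seen through the diary alone. They meet the SAE definition, sites report within 24 hours of knowing of them, and Section 9.4.3 has the study nurse complete adverse events from the clinical file and worksheet. Read strictly, item 14 assigns only the reasons for admission to the diary. Ascertainment is also better than one table cell suggests:

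- Section 4.8 asks those who stop study drug to keep attending to Week 12.
- Section 8.11 schedules withdrawal assessments, and Table 6-1 includes diary review among them.
- Section 8.12 continues outcome and economic data to 12 weeks unless consent is withdrawn, and says that the weekly calls yield economic outcomes.
- Secondary efficacy analysis is at 12 weeks (Section 3.1), which matches the diary window.
- No analysis plan is shown, and rate denominators are commonly left to it.

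Most of this stands. A reader might infer that admissions have no other source, or that the rates run 20% to 40% low. The documents support neither. The second record exists, and the upper figures need a denominator that the plan does not assign, or no diary at all from the 10.

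The choice of source remains open. Section 6.7 has participants record the admissions and length of stay themselves, and nothing designates SAE or medical-record data for this endpoint, although the next two items do name the medical record. Exit and later visits help those able to attend, not those who die first. SAE records do not capture GP, nurse, specialist or home-help contacts that are not SAEs.

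**Conclusion.** The point holds in a limited form. As specified, unplanned hospitalisation and length of stay come from a participant-kept diary when a site-held record of the same admissions already exists. Diary-based counts can therefore miss admissions close to death or withdrawal, and unequally by arm if early loss is unequal.

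The documents do not fix the size. For diary-only events the shortfall is about 7% to 20% over 12 weeks. That range assumes a constant event rate, all 50 as denominator, and departure of the 10 between baseline and Week 8. A higher rate in those who leave would raise it, and no rate is given to say by how much. Larger figures at a constant rate arise only if the 28-day follow-up enters the denominator. None of these percentages applies to admissions taken from SAE records. The unstated denominator is not a fault in itself. The primary feasibility criteria are unaffected.

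**What to change.** - In Section 5.2.1, item 14, and Section 6.7, name SAE forms and the medical record as the source for unplanned inpatient admissions, their dates and length of stay, from randomisation to Week 12 (or 24) or death. The medical record is needed because nothing shown says that the SAE form captures length of stay.
- Exclude the planned, respite, family or social admissions and pre-planned treatment that Section 9.1.5 also has recorded as SAEs.
- If Week 24 is used, check the SAE window: Section 9.1.8 describes a 4-week extension, Section 3.1 a 12-week one.
- Keep the diary for non-inpatient contacts and express those rates per day of observed diary time, for example with log diary days as an offset in a count model.
- Reconcile the blank follow-up cell in Table 6-1 with Section 8.12. If contacts are wanted for those 28 days, add a question to the four scheduled calls; if not, say that the endpoint stops at the end of treatment.

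The change is to wording and data source, with no new visits. It costs some record-abstraction time, and admissions unknown to the site may still be missed.
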